**Projet de recherche sur la santé des jeunes (PResaJe)**

**Protocol**

**Scientific responsible** : [name], PhD

Directeur de recherche Inserm

Equipe DS3

INSERM & Paris VI – UMRS 707

[name]

Email : [[contact]](mailto:[contact])

1. **Background**

Despite very advantageous health care and insurance systems, there are still major discrepancies in health status among the population. Several studies show that these disparities are correlated with socioeconomic status (Wilkinson, 1997). Poor people have higher risks of disease, morbidity (Arber, 1997) and mortality (Pappas, 1993) than the wealthier persons. This empirical result was also found for adolescents and young adults (Power, 1991). In a comparative study focusing on Britain and Finland, Rahkonen et al. (1995) find that social class differences and the level of education are two main explanatory factors of differences in health among young adults. Moreover, disparities in childhood socioeconomic circumstances have an effect on adult health and future health-related behaviors (Van de Mheen, 1998 ; Melchior, 2007 ; Poulton, 2002).

Many health professionals sustain the idea that inequalities in health access are one of the main factor explaining discrepancies in health status (Andrulis, 1998). Difficulties in financing care represents a real threat to health and well-being for persons who live in poverty. Using the fact that uninsured low-income adults in Oregon were randomly chosen to apply for Medicaid, Finkelstein et al. show that a better access to public health insurance lead to a higher health care utilization, low out-of-pocket expenditures and better health outcomes. Currie and Gruber (1996) find the same results for low-income children showing that public insurance significantly increase the use of medical care and improve child health by reducing mortality.

However, others argue that eliminating financial barriers to health care is not an efficient solution to reduce disparities in health status. In a study conducted in Canada, Dunlop et al. (2000) show that people less educated and with lower income use physicians' services at a lower rate that those with higher income and level of schooling despite the existence of an universal health care system. Health insurance coverage is not sufficient to reduce disparities in health between socioeconomic groups (Adler et al., 1993). In the RAND health insurance experiment, Manning et al. (1987) do not find effects from a better insurance coverage on health outcomes. Universal coverage do not succeed in eliminating socioeconomic disparities in health status.

This study, conducted in five Missions locales, aims at testing the efficiency of two programs. Both interventions target young unskilled people from 18 to 25 years old. The first intervention aims to optimize health coverage in order to reduce or eliminate financial barriers to health access. A social worker is in charge of finding the most advantageous coverage, assisting young people during their administrative processing and providing information on the French public health and private insurance systems. The second treatment consists on a double intervention. The first part is the same as the one described as the first intervention. But it is completed with medical consultations. Indeed, participants randomized in this group are encouraged to visit the health professionals of the structure. During these visits, GP's and psychologists are in charge of providing information on the health care system and health, doing a global health check-up and sending participants to a specialist if need be.

This randomized experiment aims at measuring the impact of the two interventions over a 12-month period. It focuses on the impact on health demand and access but also on social integration and employment.

1. **Outcomes**
   1. **. Primary outcome**

To assess impact of health issue and its screening on professional training and social autonomy of unemployed youth.

- 1. **. Secondary outcomes**

Description of health outcomes and prevention knowledge of this population aged 18 to 25 years old

To improve the content and the frequency of social and preventive medical consultations

1. **Design**
   1. **Type of study**

It will be a parallel unmasked randomised parallel interventional study.

- 1. **Participants**

***Participant identification***

Participants will be recruited among Missions locales.

5 Missions locales have been selected : Toulouse, Sénart, Clichy, Reims, Poitiers. These structures have been selected according to their interest for the study and their capacities of implementing the empirical design. Because one treatment consists of the intervention of health professionals, only *Missions locales* with a GP can take part in the study.

Any young people coming for the second time in the selected Missions Locales will be targeted in this study. Because more than a half of young people visit only one time the structure, we will select only those who will from a long-term counseling in order to reduce the attrition bias.

After finishing their meeting with their counselor, young people will go to the member of the field staff who will present the study design.

The randomization and inclusion in the study will run during one year. Each participant will be followed up during one year after completing the baseline questionnaire.

***Exclusion criteria***

Participants will be ineligible if they are unable to speak or to understand French and consequently to answer to the questionnaire (without a translator). As said before, people are included in the study after their second visit in the *Missions locales*.

People who have a serious disability that leads to special accomodations for work are not eligible in the study. Also, people who have an acute disease that lead them to have an emergency intervention will not be eligible.

***Stopping rule and lost to follow-up***

No stopping rule is planned. All the recruited participants will be included for analyses.

***Sample size***

We target a sample of 1 443 participants randomized in three groups. It means 481 participants in each group. Sample size calculations are based on the ability to detect an impact of the treatment in our outcomes.

About 55% percent of the users of the Missions locales go to a training session. To detect an increase of 10 points of each intervention with the control group (one-sided test), we need to have 409 patients in each group with a 90% power and an alpha risk of 0.05. We estimate than 15% of participants will be lost-to-follow-up, so it’s necessary to include at least 481 participants in each group.

***Randomization***

All participants are randomly allocated to one of the three groups: the first treatment group (1), the second treatment group (2) and the control group (3). Research assistants are in charge of doing the allocation to study groups by entering names and birth dates of participants in an algorithm which attributes randomly a number of cohorts (1, 2 or 3) for each participant.

Randomization occurs on receipt and signature of informed consent and baseline questionnaire. People can refuse to participate. This decision doesn’t influence the modality of counseling offered by the *Missions locales*.

***Planned timetable***

Starting date for the recruitment: november 2010

Ending date for the recruitment: november 2011

Starting date of the follow-up: november 2011

Ending date of the follow-up: novembre 2012

***Statistical analyses***

Statistical analyses will be done on Epi-Info^®^, Statview^®^ , Stata^®^, or SAS^®^. All the analyses will be transferred to the steering comitee of the study.

- 1. **Intervention**

***First intervention***

Participants randomized in the first treatment group are encouraged to meet a social worker. The main objective of this treatment is to reduce or eliminate financial barriers to health access. Taken into account the initial situation of participants regarding to the health insurance system, the social worker is first in charge of finding the most advantageous coverage among the different types of *regimes*. The social worker also assists young people in all their administrative processing with the Social Security by collecting documents necessary for subscribing for a public health coverage. He can also propose to subscribe to a private insurance or *mutuelles* for the last third which leave a co-payment not reimbursed by the public insurance. Finally, the last part of this intervention consists of providing basic knowledge on the French health care and insurance systems.

***Second intervention***

Participants randomized in the second treatment group benefit from the first intervention described above but, in addition, they are also encouraged to visit health professionals working in the *Missions locales*.

These consultations with the GP aim first at investigating the young's health status, his level of health services' use and sending him to specialist in case of need. If the first appointment is systematic, participants are free to decide the frequency of the next consultations. The main goal of this second treatment is to encourage health-related behaviors among young adults by giving useful advices, increase comfort with the health care system and their belief in its capacity to satisfy their expectations.

***Control group***

Participants in the control group benefit from the normal program offered by the *Mission locale* as both experimental groups. They are not encouraged to meet health professionals or social workers. But in case of need, they can take an appointment with health professionals.

- 1. **Recruitment and training of field staff**

***Research assistants***

Five research assistants, one for each study site, will be recruited and trained during several sessions. The first sessions aim at presenting the study protocol. Indeed, research assistants are in charge of implementing the protocol in their site. They will also be trained on the baseline and the 12-months questionnaire. Questionnaires will be administered during a face-to-face interview with the participants. Research assistants have to be trained on the way of conducting a survey.

***Social workers***

Three part-time social workers will be also recruited, one for the *Missions locales* located in Toulouse, Reims and Poitiers. For the two remaining *Missions locales* (Clichy and Sénart), the research assistants will assume the functions of social worker. In fact, these two *Missions locales* are smaller and receive less young people than the three others. Research assistants will have enough time to assume the two missions. Social workers will be trained during one session. The main goal of this training will be to harmonize interventions conducted in the five experimental sites. The study involves homogenizing practices and the content of the provided information. The training aims also at defining a common way of coding the pre- and after-treatment health coverage status of each participant in order.

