***Satisfaction of the meeting with the social worker in the ML***

The question of this section aims at investigate the level of satisfaction of the meeting with the social worker, the positive and negative aspects of this meeting.

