**Beck hopelessness scale**

To finish, we ask all the items of the hopelessness scale to calculate a score that predicts a suicide risk.

1. Data collection, validation, capture and archivage

Data will be collected in a face-to-face questionnaire by research assistant. In each Mission Locale, a person will be chosen for the study monitoring (recruitment, follow-up, lost-to-follow up, late, …). All the data will be informatically captured on an Excel file. After recruitment, all participants will have a number randomly attributed by an alogrithm. The correspondence between numbers and names of participants will be kept by the research assistant and the doctor on a paper (but not on computers). On computer, the data will be only registered with the number of the participant. All the analyses will present only agregated results. The computers that will be used for the data captures won’t be the sames that are used in Missions Locales and will be locked by a personnal password.

All the questionnaires will be kept under key in the office of [name] (located in the Faculté de médecine Pierre et Marie Curie [name]) for 15 years and will be available for the study responsibles and the promotor of the study.

All the scientific publications will have to be authorized by the scientific responsible, [name].

1. Ethics

This study will be conducted according to the last update version (Edimbourg) de la Déclaration d'Helsinki, the recommandations in ethics and good practice in epidemiology adopted in 1999 by l'Association des Epidémiologistes de Langue Française [ADELF 1998], in its updated version of 2008. This protocol has a favourable advice of CNIL (Commission nationale informatique et libertés -number 1527880).

In each Mission locale, a poster will present the study.The signature of the informed consent will be receipt by the research assistant. This consent will remind the background and objectives of the study, the medical data that will be collected, the study duration, the individual beneficies of the study, and the referent person to apply the right to object or modification.

1. Study organisation

The steering committee will be composed of

- Equipe DS3 represented by [name] and [name]

- Mission locale de Sénart represented by [name], [name], [name]

- le CREST (centre de recherche en économie et statistique) represented by [name] [name] and [name].

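### At Clichy and Sénart the person who delivers the social-worker intervention also conducts the 12-month outcome interview, an unmitigated risk of interviewer bias of unknown size

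*Protocol*

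**What the plan says.** All references are to the protocol.

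- **Research assistants:** "Five research assistants, one for each study site, will be recruited and trained during several sessions". On their tasks: "They will also be trained on the baseline and the 12-months questionnaire". The same section says that questionnaires are administered in face-to-face interviews.
- **Data collection, validation, capture and archivage:** "Data will be collected in a face-to-face questionnaire by research assistant".
- **Social workers:** Toulouse, Reims and Poitiers each get a part-time social worker. At Clichy and Sénart, "the research assistants will assume the functions of social worker". The reason given is that these sites are smaller, so the assistants have time for both jobs.
- **First intervention** and **Second intervention:** the social worker's help is the whole of the first intervention and one part of the second. Under **Control group**, participants are not encouraged to see a social worker.
- **Endline questionnaire:** participants report training (questions 18 to 20), work, use of and access to care, and coverage. A further section "aims at investigate the level of satisfaction of the meeting with the social worker".
- **Type of study:** the trial is unmasked.

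The protocol names no independent or masked interviewer and no check of the answers against records.

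**The concern.** At two sites the interviewer's relation to the participant differs by arm. A participant in arm 1 or 2 may be answering the person who helped with his or her health coverage. A control participant is answering someone who was not meant to give that help. The interviewer also knows who was helped and has a personal interest in how well the help worked.

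Training attendance is the outcome on which the sample size is based, and it is collected as an answer in this interview. If helped participants answer more favourably, or if the provider probes or records their answers differently, the arm difference moves for reasons unrelated to the intervention. The more plausible direction is towards the intervention arms, which is also the direction of the one-sided test.

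The clearest case is satisfaction with the social worker. At these two sites the participant gives that rating to the person being rated.

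**Working it through.** **Who does what.** Setting the sections side by side:

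| Task | Toulouse, Reims, Poitiers | Clichy, Sénart |
|---|---|---|
| Runs the allocation algorithm | research assistant | research assistant |
| Delivers the social-worker help (arms 1 and 2) | separate social worker | research assistant |
| Conducts the 12-month interview | research assistant | research assistant |

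Only the middle row separates the two groups of sites. The problem is delivery followed by interview.

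**The plan's own sample size (background check).** Inputs from the section Sample size: 55% against 65%, one-sided alpha 0.05, 90% power, 15% loss. With pooled variance under the null and no continuity correction,

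n = [z(0.95)·√(2·p̄·(1−p̄)) + z(0.90)·√(p₁(1−p₁) + p₂(1−p₂))]² / (p₂−p₁)²

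= [1.645·√0.48 + 1.282·√0.475]² / 0.01 ≈ 409.2.

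This agrees with the stated 409 (410 if rounded up). Then 409/0.85 = 481.2 and 3 × 481 = 1,443. The stated figures are reproduced, and this point does not change them.

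**Number exposed.** The protocol gives no recruitment share for the two sites. I assume 20%. Equal recruitment at all five sites would give 40%, which is a ceiling because the two sites are described as smaller. Only arms 1 and 2 receive the social-worker help:

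- 20% share: 0.20 × 1,443 × 2/3 ≈ 192 participants
- 40% share: 0.40 × 1,443 × 2/3 ≈ 385 participants

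**Illustrative shift.** Let w be the share of the sample at the two sites and b the excess reporting of training in arms 1 and 2 there (assumed). The pooled difference between an intervention arm and control shifts by w × b. The rejection rate with no true effect follows from 409 per arm, a true rate of 55% in both arms, and an apparent intervention rate of 55% plus the shift d:

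Φ{[d·√409 − 1.645·√(2·p̄·(1−p̄))] / √(p₁(1−p₁) + p₂(1−p₂))}

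For w = 0.20 and b = 10 points, d = 0.02 and p̄ = 0.56: (0.404 − 1.155)/0.702 = −1.07, giving 14.3%.

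For w = 0.40 and b = 10 points, d = 0.04 and p̄ = 0.57: (0.809 − 1.152)/0.700 = −0.49, giving 31.2%.

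| Share w | b = 0 | b = 5 points | b = 10 points | b = 15 points |
|---|---|---|---|---|
| 20% | 0 points; 5% | 1.0; 8.7% | 2.0; 14.3% | 3.0; 21.8% |
| 30% | 0 points; 5% | 1.5; 11.3% | 3.0; 21.8% | 4.5; 36.5% |
| 40% (ceiling) | 0 points; 5% | 2.0; 14.3% | 4.0; 31.2% | 6.0; 53.7% |

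Each cell gives the shift in points and the one-sided rejection rate with no true effect. The values of b are assumptions; nothing in the protocol fixes them.

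**The case against.** The strongest reply is that the protocol shows a dual role, not a bias. A reader might infer that outcomes at these sites are biased towards the intervention. The protocol supports only a risk: neither its size nor its direction can be derived from it. There are reasons to expect modest over-reporting. Participants are only encouraged to see the social worker, so some in arms 1 and 2 will have had no help. The help concerns health coverage, not training. Training is also asked as kind, number of sessions and days, which is harder to inflate than an opinion. All of this stands, and it is why the figures above are illustrations.

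Other stronger readings also fail:

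- **Allocation as a source of bias.** The research assistant runs the allocation at all five sites, by algorithm, after consent and the baseline questionnaire. This adds only that the interviewer knows the arm.
- **All outcomes self-reported.** GPs complete a medical questionnaire, and coverage status before and after the intervention is coded under a common scheme. At these two sites, however, the social worker trained in that coding is again the research assistant, and the sizing outcome remains self-reported.
- **Better tracing of arms 1 and 2.** Follow-up monitoring falls to a person chosen in each Mission locale, who is not said to be the research assistant. Better tracing would have no fixed direction in any case.
- **Satisfaction results uninterpretable as a whole.** Satisfaction with the doctor does not concern the interviewer. Satisfaction is also not a listed primary or secondary outcome.

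None of these points supplies a safeguard. The small size of the two sites explains the workload but does not address the bias. The endline as described already puts training and work before the satisfaction sections, but question order cannot help when the interviewer was the provider.

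**Conclusion.** The point holds as an unmitigated design risk at two of the five sites: one person delivers the social-worker intervention and then collects the self-reported outcomes of those who received it, unmasked and face to face. Interviewer and social-desirability bias would probably favour the intervention arms, by an amount that the protocol does not allow one to calculate.

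Assuming a 20% share and 10 points of over-reporting, the shift is 2 points against a 10-point target, and the rejection rate with no true effect rises from 5% to about 14%. At the 40% ceiling the figures are 4 points and about 31%. Both rest on the assumed over-reporting, and without differential reporting there is no shift. Ratings of the social worker at these sites are compromised without any such assumption, because the person rated asks the question. The risk deserves correction because the correction is cheap; it does not invalidate the trial.

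**What to change.** 1. At Clichy and Sénart, have the 12-month interview done by an existing research assistant from another site, who did not deliver the intervention there and is not told the arm. For example, the Clichy and Sénart assistants could exchange sites for the endline. Keep the interview face to face and use the same arrangement for all three arms, so that neither mode nor interviewer differs by arm.
2. Specify a sensitivity analysis that repeats the primary comparison without these two sites.
3. If interviews cannot be exchanged, report satisfaction with the social worker separately for the sites where the interviewer was the provider.

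**Cost.** No new staff, but travel and scheduling. An unfamiliar interviewer may slightly reduce retention, for which the plan allows 15% loss. The list linking names to numbers is kept on paper by the research assistant and the doctor, so the visiting interviewer needs controlled access to it. Masking will be imperfect, since a participant may reveal the arm.

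The sensitivity analysis is less precise. By the sample-size formula above, a 20% share leaves 0.8 × 409 ≈ 327 per arm and power of Φ[(0.1·√327 − 1.140)/0.689] ≈ 83%. At 40% it leaves about 245 per arm and power of about 73%. It should be read as a check on the main result, not as a second test.

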***Health professionals***

The second treatment implies the interventions of health professionals. In order to reduce the cost of interventions, we select only *Missions locales* which already employ doctors and psychologists. Psychologists accept to participate in two sites (Toulouse and Sénart). A meeting with GP’s will be organized. Because each GP has his one practice of medicine, the first objective, as for social workers, will be to harmonize the content of their interventions. GP’s will also be in charge of a part of the data collection by filling in a medical questionnaire. In fact, some information about participants’ health status will be directly collected by health professionals during the consultation. Doctors will be trained on the medical questionnaire.

***Pilot phase***

A pilot phase will take place during three months. During this pilot, the field staff will be trained. Several training sessions for the different actors of the project will be organized by the study team.

The protocol will be tested in each experimental site and adapted to fit with the specificities of the five *Missions locales*. Indeed, each *Mission locale* has its own organization. The main difficulty will be to implement a harmonized protocol in spite of particularities of the five experimental sites. Some adjustments will be needed.

A phase of coordination will be also necessary to ensure the support of members of the *Missions locales*’ staffs. They will have to be informed on the objectives of the study, the design and the methods used by the project team. We will ensure that they will not interfere with the study. The pilot will give also the possibility to test baseline and medical questionnaires.

1. **Outcomes measures**
   1. **Baseline questionnaire**

This survey instrument is designed by the study team by adapting different modules from existing survey. Different versions of this baseline survey will be tested by research assistants on young people visiting the *Missions locales* during the pilot phase. Data will be collected pre intervention.

